## Abstract

**Background:**

As more men survive a diagnosis of prostate cancer, alternative models of follow-up care that address men’s enduring unmet needs and are economical to deliver are needed. This paper describes the protocol for an ongoing evaluation of a nurse-led supported self-management and remote surveillance programme implemented within the secondary care setting.

**Methods/design:**

The evaluation is taking place within a real clinical setting, comparing the outcomes of men enrolled in the Programme with the outcomes of a pre-service change cohort of men, using a repeated measures design. Men are followed up at four and 8 months post recruitment on a number of outcomes, including quality of life, unmet need, psychological wellbeing and activation for self-management. An embedded health economic analysis and qualitative evaluation of implementation processes are being undertaken.

**Discussion:**

The evaluation will provide important information regarding the effectiveness, cost effectiveness and implementation of an integrated supported self-management follow-up care pathway within secondary care.

**Electronic supplementary material:**

The online version of this article (10.1186/s12885-017-3643-4) contains supplementary material, which is available to authorized users.

## Background

The number of people surviving after a diagnosis of cancer has increased dramatically in recent years, and is continuing to rise [1, 2]. For prostate cancer, an illustration of the 10 year survival rate is 84% in England and Wales [3] and 98% in the United States [4]. Cancer survivors are often left with challenging symptoms and side effects of treatment and with psychosocial concerns [5, 6]; specifically, prostate cancer survivors experience a range of physical symptoms, psychological and emotional difficulties and issues related to sexual function, such as impotence [7].This is presenting challenges for health care systems, in providing suitable follow-up care for those who have completed treatment [5, 8], and there is a need for more sustainable models of follow-up care which deal with capacity issues but also better address men’s survivorship needs.

In recent decades, a range of alternative follow-up care delivery models have been explored, including nurse led care, general/family practitioner led care, shared care, and patient initiated care [9]. Evidence suggests that these models are equivalent to the traditional clinic model in detection of recurrence and patient satisfaction [9]. In addition, a variety of psychosocial interventions have been developed to address men’s unmet survivorship needs, which appear to show some benefit for the men involved [10–12].

Within the last decade there has been recognition of the value of a self -management approach for cancer survivors [13]. In the United Kingdom (UK), the National Cancer Survivorship Initiative (NCSI) has promulgated an integrated, risk stratified and individualised model of cancer survivorship care, involving supported self-management and remote monitoring for the large proportion of cancer survivors who are at low risk of recurrence [14]. Such a model has recently been recommended for implementation in England by 2020, although a detailed model for prostate cancer remains to be developed and tested [15]. There is recognition of the international relevance of the principles of the model and its influence on programmes of care internationally [8].

Within this context a service improvement initiative, the TrueNTH Supported Self-Management and Follow-up Care programme (described henceforth as the Programme), has been funded in the United Kingdom by the Movember Foundation, in partnership with Prostate Cancer UK. The aim of the Programme is to implement a sustainable model of follow-up care within secondary care, based on the principles of risk stratification, supported self-management (SSM) and remote surveillance, to provide person-centred care through which to address men’s survivorship needs. The implementation of the Programme is accompanied by a comprehensive evaluation to assess effectiveness, cost effectiveness and implementation. This paper documents the evaluation protocol.

### The Programme

The Programme delivers personalised survivorship care through assessment of need, enhancement of men’s knowledge, skills and confidence to self-manage and easy access to advice and support. A stratified pathway approach [14] is employed, recognising that a proportion of post-treatment patients will be suitable for SSM.

The Programme was designed by a multi-disciplinary team, including urology health care professionals, experts in self-management techniques, and survivors of prostate cancer. The design team drew on previous work on the redesign of cancer follow-up care [14, 16] as well as the broad cancer survivorship and self-management literature. Urology and oncology teams at two National Health Service (NHS) Trusts were involved in the development of the clinical criteria used to judge suitability of men for the Programme and in piloting the Programme to assess feasibility and acceptability for both men and the clinical team.

Figure 1 details the components of the Programme and its underlying principles. The Programme is initially aimed at men being treated with radical prostatectomy, radiotherapy, or primary androgen deprivation therapy (PADT). Men are assessed for suitability at a post treatment clinic appointment with their consultant or Clinical Nurse Specialist (CNS), using clinical criteria including specified prostate specific antigen (PSA) levels for each treatment type, together with clinician assessment and discussion with the patient that they are functionally and emotionally suitable for SSM and remote surveillance. Men are first assessed for suitability from 6 weeks post radical prostatectomy and radiotherapy, or 3 months post commencement of PADT.

**Fig. 1 Fig1:**
[figure not shown]
Components of the programme and underlying principles

If a man is suitable for the Programme, this will be their last clinic appointment. Henceforth, they are monitored remotely by the specialist team, with a system of rapid re-access to clinic if indicated. There is the addition of a Support Worker role to the team, who is the mainstay of programme delivery, acting as coordinator of a man’s post treatment care and first point of contact for men who have queries or concerns, facilitating referrals to health and community resources. Men meet with the Support Worker at this point and are introduced to the Programme.

Soon after their entry into the Programme (ideally within 6 weeks), men attend a 4 h Supported Self-Management workshop, to prepare them for self-management and remote monitoring of their prostate cancer follow-up care, with a focus on living well after cancer treatment, promoting healthy lifestyles and setting personal health and wellbeing goals. Men complete a holistic needs assessment (HNA) during the session. Each workshop usually comprises between eight and 10 men and is facilitated by the CNS and Support Worker, who have been trained in workshop delivery skills and follow a facilitator manual. The workshops are based on principles of andragogy [17], Bandura’s social learning theory [18] and Adair’s action-centred leadership model [19].

The Support Worker initiates a follow-up telephone consultation after the workshop, to check that the man has grasped the main points put forward in the workshop and to answer any questions. A care plan is drawn up if appropriate. Contact with the man beyond this initial telephone call is negotiated individually, with the expectation that some men will need more contact and support for self-management than others.

Self-management and remote monitoring are facilitated by a bespoke Patient Online Service, which has both patient and health care professional facing functions. Men can access personal information such as treatment summaries and care plans, as well as validated sources of information to support self-management. They can submit their HNA and can have a two way conversation with a member of their clinical team via a secure system. The system prompts men when blood tests are due and men can see their PSA test results promptly. The health care team run virtual clinics through an electronic PSA tracking system which is interfaced with the Patient Online Service, reviewing PSA test results and HNAs, re-calling to clinic a man who has any indicators for concern.

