##### Sample size calculation

The sample size was calculated to achieve at least 90% power in two sided tests for variables which achieve a moderate intervention effect (0.3 or larger). This would require a sample of 235 participants per group and we therefore aimed to recruit around 300 men to each arm of the study, allowing for 20% being lost to follow-up by the 8 month assessment.

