##### Data analysis

Data analysis will follow a pre-specified data analysis plan. Analyses will be conducted on an ‘intention to treat’ basis. We will first describe the baseline characteristics of participants at time T0 within each group and will compare clinical and demographic characteristics and outcome measure scores of the two groups. The same comparisons will be made with baseline data between those continuing to four and 8 month follow-up and those lost to attrition.

A regression analysis will be conducted for each of the outcome measures at the 4 month and 8 month time points separately, controlling for study site, the outcome in question if available at T0, and baseline co-variates including age, type of treatment, educational attainment, time since diagnosis, domestic status, co-morbidity, employment status, and ethnic status. If other factors differ between groups at baseline, additional controlled analyses will be carried out.

We will also estimate a mixed model including outcome at four and 8 months simultaneously, including an interaction to give separate estimates of the Programme versus standard care comparison at each follow-up point.

Finally, we will investigate whether there are any distinct subgroups for whom the intervention is effective. Guided by existing literature to indicate likely subgroup effects, separate regression analyses will be conducted for older versus younger men, men with and without co-morbidities, and men with higher and lower levels of deprivation. We will address subgroup analyses within the context of regression modelling (either linear or logistic). Interaction terms between each specified dichotomous factor (indicating subgroups) and the Programme versus standard care factor will be examined. Where interaction terms achieve statistical significance (at the 5% level), we will examine separate Programme versus comparator group estimates for each subgroup. All subgroups analyses will be considered exploratory in nature.

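### Group workshops in the Programme arm only are not allowed for in the sample size or in any analysis the article describes, so standard errors are too small if outcomes correlate within workshops

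*Protocol article*

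**What the plan says.** The Programme section describes a single 4-hour workshop soon after entry: "Each workshop usually comprises between eight and 10 men and is facilitated by the CNS and Support Worker". The Comparator group section describes standard follow-up in clinic or by telephone, with no group session.

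The Sample size calculation section says: "The sample size was calculated to achieve at least 90% power in two sided tests", for an effect of 0.3 or larger. It continues "This would require a sample of 235 participants per group", and after a 20% allowance for loss, "we therefore aimed to recruit around 300 men to each arm of the study". It mentions no ICC or design effect.

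The Data analysis section says: "A regression analysis will be conducted for each of the outcome measures", at 4 and 8 months separately, controlling for site, the T0 value of the outcome and a list of baseline covariates. A mixed model then takes both follow-up times together. The economic Analysis section uses ordinary least squares with White standard errors for QALYs, and a bootstrap with replacement for uncertainty. None of these descriptions mentions workshop membership. The Data analysis section also refers to a pre-specified analysis plan, which is not shown.

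**The concern.** Men who sit in the same workshop share facilitators, discussion and each other's company. The article bases the workshops partly on social learning theory, so some influence of group members on one another is intended. Outcomes such as unmet need, activation and health behaviours may therefore be positively correlated within a workshop. The treatment creates this grouping in one arm only, which is a partially nested design.

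The terms the article names do not deal with it:
- Site adjustment removes differences between sites, not between workshops within a site.
- Adjusting for T0 cannot remove correlation that arises later, in the workshop.
- A mixed model over two time points handles repeated measures within a man, not men within a workshop.
- White standard errors allow for unequal variances but still take men as independent.

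At stake are confidence intervals that are too narrow and false-positive rates above the nominal level, on the primary outcome and on any other outcome with a positive workshop ICC. The power figure also rests on an assumption that is not stated.

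**Working it through.** **Inputs from the article.** Two-sided test, 90% power, effect 0.3 (read as a standardised difference, SD = 1), 235 analysed per group, 20% loss, workshops of 8 to 10.

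**Inputs assumed.**
- Alpha 0.05. The sample size section gives none. The Data analysis section uses 5% for interactions ("Where interaction terms achieve statistical significance (at the 5% level"), and 0.05 reproduces the stated figure.
- Workshop ICC 0.01 to 0.10.
- Analysed men per workshop, m = 5 to 9. Nine is the midpoint of attendance. Five allows for loss to follow-up and for attenders who are not in the evaluation.

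**Step 1: reproduce the plan's figure.** The two-sample t-test for independent men, d = 0.3, 90% power, two-sided 5%, needs 234.46 per group, rounded up to 235. Then 235/0.8 = 294, stated as around 300. Recruiting 300 leaves 300 × 0.8 = 240, about 5 men per arm to spare. The target therefore contains no real allowance for clustering.

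**Step 2: add workshops in one arm.** The design effect in the Programme arm is DE = 1 + (m − 1) × ICC. With n = 235 per arm:
- Independent-data SE = √(2/235) = 0.0923
- Ratio of correct to independent-data SE: R = √((1 + DE)/2)
- True error of a nominal 5% test = 2 × (1 − Φ(1.96/R))
- Power = Φ(0.3/(0.0923 × R) − 1.96)

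Example, m = 9, ICC 0.05: DE = 1 + 8 × 0.05 = 1.40; R = √(2.40/2) = 1.095; error = 2 × (1 − Φ(1.789)) = 7.4%; power = Φ(2.969 − 1.96) = 84.3%.

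| m | ICC | DE | R | True error | Power, unadjusted |
|---|---|---|---|---|---|
| 5 | 0.01 | 1.04 | 1.010 | 5.2% | 89.6% |
| 5 | 0.02 | 1.08 | 1.020 | 5.5% | 89.0% |
| 5 | 0.05 | 1.20 | 1.049 | 6.2% | 87.3% |
| 5 | 0.10 | 1.40 | 1.095 | 7.4% | 84.3% |
| 9 | 0.01 | 1.08 | 1.020 | 5.5% | 89.0% |
| 9 | 0.02 | 1.16 | 1.039 | 5.9% | 87.9% |
| 9 | 0.05 | 1.40 | 1.095 | 7.4% | 84.3% |
| 9 | 0.10 | 1.80 | 1.183 | 9.8% | 78.5% |

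**Step 3: credit for baseline adjustment.** The planned regressions adjust for the T0 outcome where it exists; the sizing takes no credit for this. With baseline correlation r (assumed), multiply the SE by √(1 − r²). At m = 9:
- r = 0.5: power 92.9% at ICC 0.05 and 88.8% at ICC 0.10
- r = 0.3: power 87.5% and 82.2%

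These figures shrink the workshop variance along with the rest. If it arises wholly after T0 and does not shrink, the SE is √((2(1 − r²) + (m − 1) × ICC)/235), and r = 0.5 gives 91.6% and 85.8%. In either form the analysis must still model the workshops for its standard error to be right.

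**The case against.** A reader might infer that the planned models definitely treat men as independent. The article does not establish that. It defers to an analysis plan that is not shown, and an article commonly leaves the variance structure to such a plan. What stands is that the article names no workshop term, and that an unseen plan cannot change the basis on which 235 was derived.

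A reader might also infer that the trial is underpowered, or that the 90% holds only with a zero ICC. That is true of the unadjusted calculation, but not necessarily of the planned analysis, because baseline adjustment may restore the power.

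The ICC may well be low. The workshop is one session run to a manual. The article treats the Support Worker role as the core of delivery, and the telephone consultation, later contact, remote monitoring and online service are individual. Calling the workshop the main active component would go beyond the text. Outcomes are measured at 4 and 8 months, and the ICC would differ between outcomes as unlike as urinary symptoms and activation.

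Comparator men also share clinicians, so clustering may not be confined to one arm, and site adjustment absorbs part of any shared-staff effect. Nine analysed men per workshop is an upper-end figure, since attendance is not the same as enrolment and retention. These points limit the size. They do not remove the correlation between workshops within a site.

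**Conclusion.** The point holds conditionally. The sample size makes no allowance for workshop clustering, and no analysis the article describes names it. For any positive workshop ICC, standard errors that ignore it are too small.

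Over the assumed ranges in the table, the correct standard error is about 1% to 18% larger and the true type I error about 5.2% to 9.8%. Unadjusted power at 0.3 is about 90% down to about 78%. At ICC 0.01 the effect is negligible; with nine men per workshop it becomes material from about 0.02 to 0.03. The mechanism is well supported, but the magnitude rests on an ICC and a cluster size that the document does not supply. The standard error is the firmer half of the point; a loss of power below 90% in the planned adjusted analysis is not shown. This is a cheap improvement rather than a fatal flaw.

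**What to change.** Unless the analysis plan already does so:

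1. Fit a partially nested model: a workshop random effect in the Programme arm only, with comparators and non-attenders as singletons, and small-sample degrees of freedom. Workshop-clustered standard errors are an acceptable alternative.
2. In the economic evaluation, replace White standard errors with workshop-clustered ones, and resample by workshop in the Programme arm of the bootstrap.
3. State that the 90% assumes no workshop clustering and takes no credit for baseline adjustment, and show power over a range of ICC and cluster size as above.

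The cost is slightly wider intervals and a less favourable unadjusted power figure; no more men are needed. Workshop attendance must be obtained from the sites. The article does not list it among the data collected, so its availability should be confirmed first.

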## Methods/design

### Setting

The service re-design is being evaluated in four prostate cancer treatment centres within the NHS in England. Three sites were selected following an expression of interest process. Criteria for selection included enthusiasm of the clinical team, capability of IT departments to implement the proposed IT solution, and inclusion of hospitals in both urban and rural locations. The fourth site had previously been involved in development of the clinical criteria and piloting work, and was added as an evaluation site after 5 months of recruitment in order to boost numbers.

### Design

A mixed methods design is being implemented to assess the value of the Programme and to understand processes of implementation. The evaluation aims to: 1) assess the effectiveness of the Programme across key outcomes 2) assess the impact of the Programme on costs 3) assess the process of implementing the Programme, in order to identify any facilitating and inhibiting factors.

#### Evaluation of effectiveness

##### Design

The effects of the Programme on patient outcomes are being assessed by comparing the outcomes of men enrolled in the Programme with the outcomes of a pre-service change cohort of men, using a repeated measures design. The evaluation takes a pragmatic approach, testing the effectiveness of the Programme in a real clinical setting, allowing for clinical judgement in assessing men’s suitability for the new service and for flexibility in service delivery [20].

##### Comparator group

The comparator group is a pre-service change group of men, recruited from the cohort of men in prostate cancer follow-up care at the four sites during the period immediately prior to the introduction of the Programme. The comparator group men receive their hospital’s standard follow-up care (standard care) as it was before the service change; this is either clinic based follow up with a urological surgeon, oncologist or CNS, or telephone follow up with a CNS.

Where capacity allows, men in the comparator group are migrated to the new service once they have completed their final study questionnaire.

##### Eligibility

Men are eligible to enter the evaluation if they are: i) within 3 years of completion of radical prostatectomy/radiotherapy or within 3 years of commencement of PADT ii) are 18 years of age or older and iii) have adequate English language ability to complete study questionnaires. Men who are unable to give informed consent and men participating in clinical trials which require face-to-face contact are excluded.

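### Programme men pass a suitability assessment that is not stated for comparator men, so the comparison may not be like with like

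*Protocol article*

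**What the plan says.** **Entry to the evaluation (Protocol article, Eligibility).** Men must be "within 3 years of completion of radical prostatectomy/radiotherapy or within 3 years of commencement of PADT", aged 18 or over, and able to complete the questionnaires in English. Men who cannot consent, or who are in trials needing face-to-face contact, are excluded. These rules cover both groups. The Recruitment section refers to them and to no others.

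**Entry to the Programme (The Programme).** The section expects that only "a proportion of post-treatment patients will be suitable for SSM". Men are assessed "using clinical criteria including specified prostate specific antigen (PSA) levels for each treatment type", and clinician and patient must also agree that the man is "functionally and emotionally suitable for SSM and remote surveillance". There is a lower time limit: "Men are first assessed for suitability from 6 weeks post radical prostatectomy and radiotherapy, or 3 months post commencement of PADT". The consequence is stated after Figure 1: "If a man is suitable for the Programme, this will be their last clinic appointment".

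**The contrast (Evaluation of effectiveness, Design).** The effect is assessed by "comparing the outcomes of men enrolled in the Programme with the outcomes of a pre-service change cohort of men". The Comparator group section draws that cohort from men in prostate cancer follow-up at the four sites just before the change, and states no suitability condition.

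**The analysis (Data analysis).** "Analyses will be conducted on an ‘intention to treat’ basis". The regressions control for site, the outcome at T0 where there is one, age, treatment type, education, time since diagnosis, domestic status, co-morbidity, employment and ethnic status. Further analyses follow if other factors differ at baseline.

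**The concern.** One group is defined by having passed an assessment. The other, as described, is defined only by being in follow-up. The assessment concerns disease status, function and emotional state, which plausibly relate to the outcomes: unmet need (primary), GHQ-12, EQ-5D-5L and service use. If men who would not pass are absent from the Programme group but present in the comparator, the Programme group could look better and cheaper with no effect of the Programme.

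The intention-to-treat statement does not address this. It governs what happens to men after they are in a group, whereas here the selection decides who is in the group. The Discussion concedes that the comparator is non-randomised and relies on adjustment for known confounders, but does not mention this selection step, which is part of the intervention's design.

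**Working it through.** **1. Entry conditions side by side**

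| Condition | Programme group | Comparator group |
|---|---|---|
| Within 3 years of treatment | yes | yes |
| Age, English, consent | yes | yes |
| No trial needing face-to-face contact | yes | yes |
| PSA level by treatment type, other clinical criteria | yes | not stated |
| Functional and emotional suitability | yes | not stated |
| Minimum time since treatment | yes (6 weeks or 3 months) | not stated |

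**2. What the planned adjustment covers.** The T0 outcome, co-morbidity, age and treatment type will each carry part of the difference. PSA, suitability and time since treatment are not among the listed covariates; time since diagnosis is a different interval. Stage and grade are collected (Data collection) but not listed as covariates. PSA is not in that section's list of record items. Table 1 places health service use at T1 and T2 only, so it has no T0 value to adjust for. QALYs are to be controlled for baseline utility; no such control is stated for average cost per patient.

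**3. The plan's sample size.** Effect 0.3 (read as SD units), 90% power, two-sided 5% (alpha assumed):

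n = 2 × (1.960 + 1.282)² / 0.3² = 233.5, so 234 per group.

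The exact t-test gives 235 (power 0.901). With 20% loss, 235 / 0.8 = 293.75, so 294, in line with the target of about 300. The plan's figure reproduces and is not in dispute.

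**4. Illustration of bias.** The documents give neither the share of men who would fail the assessment nor how much worse they do. Assume that 10 to 30% of comparator men would fail, and that after adjustment they are 0.2 to 0.5 SD worse.

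Bias = share × gap, from 0.1 × 0.2 = 0.02 SD to 0.3 × 0.5 = 0.15 SD.

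SE = √(2/235) = 0.0923 SD. With no true effect, the two-sided rejection rate is P(Z > 1.96 − bias/SE) + P(Z < −1.96 − bias/SE):

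| Residual bias (SD) | Rejection rate |
|---|---|
| 0.02 | 5.5% |
| 0.05 | 8.4% |
| 0.10 | 19% |
| 0.15 | 37% |

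These rates use the unadjusted SE. If T0 and follow-up scores correlate at 0.5 (assumed), SE = 0.0923 × √(1 − 0.25) = 0.0799, and the same biases give 5.7% to 47%.

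**5. How far adjustment matters.** Take 20% failing and a gap of 0.5 SD before adjustment: bias 0.10 SD and 19% rejection. If adjustment removes half, 0.05 SD and 8%. If it removes three quarters, 0.025 SD and 6%.

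**6. Power if comparators are restricted.** Losing 10% leaves about 212 and losing 30% about 165, against 235 Programme men. SE = √(1/235 + 1/n):

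| Comparators | SE | Power at 0.3, unadjusted | Power with r = 0.5 adjustment |
|---|---|---|---|
| 212 | 0.0947 | 89% | 96% |
| 165 | 0.1016 | 84% | 93% |

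**The case against.** The strongest reply has four parts.

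- **Silence is not proof.** The study-flow figure is not shown and the article condenses a fuller protocol. Comparator men may later move to the Programme where capacity allows, which is compatible with their having been thought suitable. This stands: a reader might infer that the comparator definitely contains unsuitable men, but the text supports only that it may. Capacity is, however, the only condition stated for that move, so it does not show that screening took place.
- **Direction.** A reader might infer that the result must favour the Programme. Without a stated lower time limit, the comparator could also include men early in recovery, whose natural improvement would work in its favour. That too is conjecture, but it leaves the net sign open.
- **Existing adjustment.** T0 scores, co-morbidity and treatment type are controlled, other imbalances trigger further analyses, the pragmatic use of clinical judgement is openly stated, and a pre-specified analysis plan exists. This reduces the concern. It cannot reach PSA or a clinician's judgement unless these are recorded for comparator men.
- **Limits of the remedy.** Restricting on recorded criteria does not remove selection by judgement. That is correct, and the remainder has to be reported as a limitation. A preference for weighting over regression, or for another label than intention to treat, would be a matter of method or wording and is not pressed.

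**Conclusion.** The point holds in a limited form. The article makes suitability a condition of entering the Programme, compares enrolled men with the pre-change cohort, and states no matching condition for that cohort. The groups may therefore differ in ways related to the primary outcome, wellbeing and cost.

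The likely direction favours the Programme, but the net direction is not established. The size cannot be fixed from the documents: the range from about 5.5% to 37% false positives rests wholly on the assumed share and gap, and its lower end is close to the nominal level. A reader who takes only the upper figures would overstate the case. Planned adjustment removes part of the bias. Service use, which feeds the cost comparison, is more exposed because it has no T0 value.

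This should be fixed before analysis; it does not by itself invalidate the evaluation. Confidence is moderate, because a comparator suitability screen may be described in material not shown. If one took place, the article should say so.

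**What to change.** Before analysis:

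1. From the medical records already being accessed, apply the Programme's own documented objective entry criteria (PSA, any other recorded criteria, and time since treatment, all as at recruitment) to every comparator man.
2. Make Programme men against comparators who meet those criteria the main comparison. Keep the full comparator as a sensitivity analysis.
3. Add PSA, stage, grade, time since treatment, and T0 EQ-5D-5L and GHQ-12 to the adjusted models, including the cost model.
4. State the conclusion as the effect in men suitable for the Programme.
5. Name the remaining judgement-based selection in the limitations, alongside the general statement on non-randomisation.

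**Cost.** One or two further items from the records (PSA and, where not already held, the treatment date) and changes to the analysis plan. Data collection has closed, so the plan should record the reason for the change and that it was made before outcomes were compared. If 10 to 30% of comparators are lost (assumed), unadjusted power at 0.3 falls to about 84 to 89%, largely recovered by the baseline adjustment already planned.
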